## Variables

The outcome variable of this study is a change in Pelvic Organ Prolapse Symptom as measured by POP-SS and the intervention is Pelvic Muscle Training. Covariates include degree of POP, the severity of POP-SS, adherence to Pelvic Floor Muscle Training protocol, maternal age, location of POP, history of pelvic surgery, number of childbirth, level of education, body mass index, trauma, marital status, occupation, age at first marriage, age at first delivery, place of delivery, history of prolonged labor, medical conditions (chronic cough, diabetes mellitus), family history of POP, mode of delivery, duration since last menstrual period.

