## Description of Intervention

From each selected health facility, two female Nurses or Midwives will be trained on Pelvic Floor Muscle Training and how to counsel patients. The training will be given for nurses and midwives by urogynaecologist. The training will have a theory, simulation, and video aids.

Among women diagnosed to have symptomatic stage I-III pelvic organ prolapse, 136 will be assigned to the interventional and control groups based on their pre-assigned enumeration area (cluster). Those assigned to intervention will receive pelvic floor muscle training and prolapse lifestyle advice focusing on constipation, chronic coughing, heavy lifting, and other medical conditions. The control group will receive only lifestyle modification but not trained on pelvic floor muscle exercise. The detailed counselling will be provided using a translated Sidaamu Afoo version of a leaflet (Annex-IV) (22).

In the interventional group, at the initial visit, women will be informed about their stage of POP, type of prolapse (anterior, posterior, or central), the advantage of pelvic floor muscle exercise, and how it works. The detail of the exercise and follow-up schedule will be explained in detail in a private room for 30-40minutes. They will be trained to sit or lie comfortably, train pelvic muscles with 10 times 10-second maximum holds, and 10 fast contractions. This will be repeated at least three times per day (morning, afternoon, and night) (14, 22). They will be invited to attend five visits (at weeks 0, 2, 6, 10, and 15) at a nearby health facility. Five visits are preferred because 15-weeks intensive training is recommended to get adequate muscle strength) (23).

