## Data Measurements

At each visit, women's adherence to pelvic floor muscle training will be evaluated by their pelvic muscle trainer. At week two, women will be assessed for adherence to pelvic floor muscle exercise in the last two weeks (three times a day, once a day, a more than once per week, once per week, a more than one days per week). At weeks six, 10, and 15, they will be assessed for adherence to pelvic floor muscle exercise in the last four weeks using similar questions used on week two (three times a day, once a day, a more than once per week, once per week, a more than one day per week). In addition, they will be assessed for prolapse symptoms at weeks 10 and 15.

At the end of six months, the overall adherence to training protocol will be evaluated from their dairy or report of pelvic muscle trainer. Women’s adherence to training protocol is considered adequate when they complete at least 80% of the training sessions (24). This will be calculated at each visit based on the training session and finally compiled.

The primary outcome of the study is a change in prolapse symptoms measured by POP-SS. The POP-SS is the same measurement with study one which measures the frequency of prolapse symptoms in the last four weeks, measured by seven items with a Likert-scale of 0 to 4 scale (0= never felt symptom, 1= occasionally, 2= sometimes, 3= most of the time and 4= all of the time). The total score will be calculated by summing up all responses for the seven-question and the total score will range from 0 to 28, the highest value indicating the severity of prolapse symptoms (25, 26). At the end of the six months, the mean change in prolapse symptoms from the initial visit will be compared between the two groups (intervention and control groups) to measure the effect of pelvic muscle training.

The secondary outcome, women’s perceived change in prolapse symptom since the start of the intervention, will be measured as improved, the same, or worsened based on Patient Global Impression of Change (PGIC) (14, 27).

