## Data Management and Analysis

Data entry, cleaning, missing data management and descriptive data presentation is similar with Paper-II. In addition, in this paper, to assess the effect of pelvic floor muscle training on prolapse symptoms, an Intention-to-treat (ITT) analysis will be used at the end of six months of training. This analysis will include all women included in the trial study at the beginning and who attended at least one follow-up. A paired t-test will be used to evaluate the mean change from baseline for both groups (intervention and control) groups. Then independent t-test will be used to compare the mean change for the interventional groups against the mean change of the control group as an effect size. The level of significance will be set at a P-value < 0.0125 by using the Bonferroni correction formula for multiple outcomes (16, 29, 30). In this study, there are four outcomes of this single intervention, which included a mean change in prolapse symptoms and three components of prolapse quality of life (Paper IV). Therefore, the level of significance is obtained by dividing the usual P-value (0.05) by a number of statistics to be performed.

A summary of statistics will be computed both at the cluster-level and individual levels for both arms. The presence of cluster effects will be assessed and a multilevel analysis will be considered if a significant ICC value of > 0.5 is detected (31). As an alternative, since the outcome of this study is continuous data, both the cluster-level and individual-level analysis will produce the same result if the cluster size is equal. But if the cluster size is variable, an individual-level analysis weighted by cluster size will be done (20, 21).

This study will use stratified cluster randomization based on geographical locations. This may not balance all possible confounders, especially individual-level factors that may vary across strata. Therefore, the statistical technique of confounder control will be used to control possible confounders at the analysis stage. A Linear Mixed-Effect Model will be used to control confounders in multivariable linear regression. This analysis can increase the statistical power and preferable than the general equation estimation model (GEE) (32). Multicollinarity of the independent variables will be checked before fitting the variable into multivariable linear regression in similar fashion with Paper-II.

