## Variables

The primary outcome variable of this study is a change in Health-Related Quality of Life (HRQL). The secondary outcome is participants’ perceived change in Prolapse impact on their quality of life measured by Patient Global Impression of Improvement (PGI-I) (34). The intervention is Pelvic Floor Muscle Training and other covariates include degree of POP, the severity of POP-SS, adherence to Pelvic Floor Muscle Training protocol, maternal age, location of POP (anterior, posterior or apical), number of childbirth, level of education, history of depression, need for fertility, body mass index, trauma, marital status, occupation, age at first delivery, place of delivery, history of prolonged labor, medical problem (chronic cough, diabetes mellitus), family history of POP, mode of delivery.

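### Adherence to the training is listed as a covariate for both trial outcomes, although it arises after allocation and exists only in the trained arm; the adjusted arm effect would then no longer estimate the effect of the programme

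*Protocol*

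**What the plan says.** Paper-III, Variables, names the change in POP-SS as the outcome and continues: "Covariates include degree of POP, the severity of POP-SS, adherence to Pelvic Floor Muscle Training protocol, maternal age", followed by items such as parity, education and body mass index. Paper-IV, Variables, does the same for quality of life: "other covariates include degree of POP, the severity of POP-SS, adherence to Pelvic Floor Muscle Training protocol, maternal age". Neither list confines adherence to one arm or to a secondary analysis.

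Paper-III, Data Management and Analysis, sets two between-arm analyses. The first is unadjusted: "an Intention-to-treat (ITT) analysis will be used at the end of six months of training", and "Then independent t-test will be used to compare the mean change for the interventional groups against the mean change of the control group", at a significance level of 0.0125. The second is adjusted, because stratified allocation may leave individual-level factors unbalanced: "A Linear Mixed-Effect Model will be used to control confounders in multivariable linear regression". Paper-IV adopts the same procedure. The section does not itemise the model terms.

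On the arms, Paper-III, Description of Intervention, says: "The control group will receive only lifestyle modification but not trained on pelvic floor muscle exercise". On measurement, Paper-III, Data Measurements, says that at each visit "adherence to pelvic floor muscle training will be evaluated by their pelvic muscle trainer", with an overall figure compiled at six months from the diary or the trainer's report. Adherence counts as adequate at 80% or more of the training sessions. No adherence measure is planned for controls.

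**The concern.** A confounder in a trial model should be fixed before allocation. Adherence to the training is a consequence of being allocated to it, and is one route by which it would work. Conditioning on it takes out that part of the effect.

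The structure makes this worse, because adherence varies in one arm only. If controls are coded 0, the arm coefficient is the difference between a trained woman at zero adherence and a control. That quantity does not answer either paper's objective and does not fit the intention-to-treat principle the plan adopts.

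At stake is the adjusted result for POP-SS and for each P-QoL component. It could sit near zero, or be very imprecise, beside a clearly positive t-test. With four clusters per arm, and with the plan itself doubting that allocation will balance individual factors, readers are likely to give the adjusted result weight.

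**Working it through.** **Inputs from the protocol.** Paper-III, Sample Size Determination: mean change 3.16 (SD 4.78) with training and 0.12 (SD 3.86) in control, so the effect is 3.16 − 0.12 = 3.04; 16% loss. The flow diagram gives 78 women per arm, so 78 × 0.84 ≈ 65 analysed per arm.

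**Check of the design inputs.** n per arm = (4.78² + 3.86²)(2.576 + 0.842)² / 3.04² = 47.7 at a two-sided 0.01 level and 80% power. The total after loss is 2 × 47.7 / 0.84 = 113.6, against the stated 113.4. The inputs are therefore those the design rests on. The figure itself is not in dispute here.

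**Assumptions.** The protocol gives no adherence distribution. I take two for the share of sessions completed: Beta(3.5, 1.5), with mean 0.70 and variance 0.035, and Beta(8, 2), with mean 0.80 and variance 0.01455. Controls are coded 0 and clustering is ignored.

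**What the model estimates.** With adherence A = 0 in every control, the model with arm and A amounts to a regression on A within the trained arm. The arm coefficient is that line's intercept (A = 0) minus the control mean. With the 80% indicator, it is the mean of trained women below 80% minus the control mean.

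**Bias, if benefit is proportional to adherence.**
- Continuous A: benefit at A = 0 is nil, so the arm coefficient is 0 under either distribution.
- Indicator: coefficient = 3.04 × E(A | A < 0.8) / E(A). Beta(3.5, 1.5): 3.04 × 0.596 / 0.70 = 2.59. Beta(8, 2): 3.04 × 0.689 / 0.80 = 2.62.

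If only half of the benefit runs through adherence, simulation with continuous A at 78 per arm gives 1.4 to 1.5.

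**Precision, if benefit does not depend on adherence.** There is no bias under either coding. The unadjusted SD is √[(4.78² + 3.86²)/65] = 0.76.
- Continuous A: variance = (4.78²/65)(1 + mean²/variance of A) + 3.86²/65. Beta(3.5, 1.5): (4.78²/65)(1 + 14) + 3.86²/65 = 5.50, SD 2.35, ratio 3.1. Beta(8, 2): (4.78²/65)(1 + 44) + 3.86²/65 = 16.05, SD 4.01, ratio 5.3. Simulation at 65 per arm runs slightly higher, up to about 5.4.
- Indicator: variance = 4.78²/(65q) + 3.86²/65, where q is the share below 80%. Beta(3.5, 1.5): q = 0.645, SD 0.88, ratio 1.15. Beta(8, 2): q = 0.436, SD 1.02, ratio 1.34.

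With other assumed distributions (mean 0.6, SD 0.25; mean 0.8, SD 0.15) and 78 per arm, simulation gives ratios of about 2.3 and 4.9 for continuous A.

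**Does the collinearity rule catch it?** Paper-II's rule, carried into Paper-III, omits variables with a variance inflation factor above 5. For arm and continuous A alone, the factor is 1 + mean²/(2 × variance): 1 + 0.49/0.07 = 8.0 for Beta(3.5, 1.5). Both terms have the same factor, so the rule cannot say which to omit and could remove arm. For mean 0.6 and SD 0.25 the simulated factor is 4.3, and for the indicator with 70% adequate it is 2.2; in those cases the rule does not act.

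**The case against.** The strongest reply is that the treatment effect is defined by the unadjusted t-test of mean change under intention-to-treat, and adherence does not enter it. This stands. A reader might infer that the trial's main effect estimate is destroyed; the protocol does not support that, since only the adjusted model is exposed.

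Second, the analysis section names no model terms and speaks only of confounders, so entry of adherence is inferred from the Variables lists. That is correct, and a separate analysis plan could settle the terms. But the lists call adherence a covariate without restriction, the mixed model is the only stated use of covariates, and nothing excludes it.

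Third, a reader might take total loss of the effect as the expected result. It follows only from continuous coding with benefit wholly proportional to adherence. The protocol's own summary is a threshold at 80%, under which the loss is modest (3.04 to about 2.6).

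Fourth, the collinearity rule would flag some continuous-coded models. It would, but without choosing the right term to drop.

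Finally, a reader might infer that blank control values would remove the whole control arm from a complete-case fit. That is not the stated handling: Paper-II's multiple imputation carries over to Paper-III. Imputation is no remedy, however, since it would invent training adherence for women who were never trained.

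**Conclusion.** The concern holds for the adjusted analysis of both papers and should be fixed. Adherence is a post-allocation variable defined in one arm, and including it with arm changes what the arm coefficient means.

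Under benefit proportional to adherence, 3.04 becomes about 0 (continuous) or about 2.6 (80% indicator). Under no dependence, the estimate is unbiased but its SD rises about 3- to 5.5-fold (continuous) or about 1.15- to 1.4-fold (indicator). These figures rest on the plan's effect and SDs, 65 women per arm, controls coded 0, clustering ignored and assumed adherence distributions. The change in meaning does not depend on those assumptions; the size does. The unadjusted t-test remains valid on this point, which is why it does not rank as a must-fix.

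**What to change.** Delete adherence from the covariate lists in the Variables sections of Paper-III and Paper-IV. State in the Data Management and Analysis sections that the effect model may include only variables measured before allocation, and that POP-SS severity means the baseline score, since symptoms are also assessed during follow-up. Report adherence descriptively for the intervention arm or, if a relation with outcome is of interest, in a separately labelled exploratory analysis within that arm. The cost is one term removed from two lists and a sentence or two added. Data collection, sample size and the primary test do not change.

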## Data Measurements

At each visit, women's adherence to pelvic floor muscle training will be evaluated by their pelvic muscle trainer. At week two, women will be assessed for adherence to pelvic floor muscle exercise in the last two weeks (three times a day, once a day, a more than once per week, once per week, a more than one days per week). At weeks six, 10, and 15, they will be assessed for adherence to pelvic floor muscle exercise in the last four weeks using similar questions used on week two (three times a day, once a day, a more than once per week, once per week, a more than one day per week). In addition, they will be assessed for prolapse symptoms at weeks 10 and 15.

At the end of six months, the overall adherence to training protocol will be evaluated from their dairy or report of pelvic muscle trainer. Women’s adherence to training protocol is considered adequate when they complete at least 80% of the training sessions (24). This will be calculated at each visit based on the training session and finally compiled.

The primary outcome of the study is a change in prolapse symptoms measured by POP-SS. The POP-SS is the same measurement with study one which measures the frequency of prolapse symptoms in the last four weeks, measured by seven items with a Likert-scale of 0 to 4 scale (0= never felt symptom, 1= occasionally, 2= sometimes, 3= most of the time and 4= all of the time). The total score will be calculated by summing up all responses for the seven-question and the total score will range from 0 to 28, the highest value indicating the severity of prolapse symptoms (25, 26). At the end of the six months, the mean change in prolapse symptoms from the initial visit will be compared between the two groups (intervention and control groups) to measure the effect of pelvic muscle training.

The secondary outcome, women’s perceived change in prolapse symptom since the start of the intervention, will be measured as improved, the same, or worsened based on Patient Global Impression of Change (PGIC) (14, 27).

## Data Collection Tools and Procedure

The Pelvic Organ Prolapse symptoms will be assessed using a translated and validated Sidaamu Afoo version of the POP-SS questionnaire. This tool will be obtained from Paper I of this dissertation project (Paper I). After the intervention, in addition to the POP-SS tool, the Patient Global Impression of Change (PGIC) tool will be used to evaluate patients’ perceived change in prolapse symptoms. The PGIC evaluates overall health status as perceived by the patient in a seven-point single item scale measured as 1= very much improved, 2= much improved, 3= minimally improved, 4 = no change, 5= minimally worse, 6= much worse or 7= very much worse. This scale can be classified into three major categories for description purposes: worsen or disease deterioration (very much worse, much worse, or minimally worse), the same (no change), and improved (minimally improved, much improved, and very much improved) (27). The PGIC will be translated into Sidaamu Afoo by native speakers and translated back to English to check its consistency.

After six months of intervention, the same data collectors of the baseline data will go to the house of the study participants and collect the data through face-to-face interviews. These data collectors are those who were recruited by Hawassa University to collect data from the HDSS site and fluent in Sidaamu Afoo.

## Data Quality Control

To ensure the quality of data, the tool will be translated to the local language and validated according to the protocol prior to this study. Data collectors will be trained for two days and supervised daily.

To reduce the risk of bias, the clusters will be stratified and allocated to each arm to balance both groups. Clusters from each strata will be allocated randomly by using a lottery method. A buffer zone, at least one kebele, will be used to separate the interventional clusters from the control clusters, to reduce information contamination (this will avoid the risk of diluting the effect of treatment). The post-intervention data collectors will remain blinded to the interventional and control groups until the end of the study. To reduce loss to follow-up, participants’ transportation costs and time compensation will be covered by the investigator. In the event that the patients cannot attend the visit, they will be visited at home. Their adherence to the training protocol will be recorded daily and checked at each visit. The completeness of the data will be checked daily by the supervisor; data entry will be started as soon as the data collection process is initiated. If any error is identified while checking for completeness and data entry, the data collector will go back to the specific house and correct the error. Data stratification and multivariable linear regression will be run to control for possible confounders (28). The hard copy will be stored in a private cabinet by the principal investigator.

## Data Management and Analysis

Data entry, cleaning, missing data management and descriptive data presentation is similar with Paper-II. In addition, in this paper, to assess the effect of pelvic floor muscle training on prolapse symptoms, an Intention-to-treat (ITT) analysis will be used at the end of six months of training. This analysis will include all women included in the trial study at the beginning and who attended at least one follow-up. A paired t-test will be used to evaluate the mean change from baseline for both groups (intervention and control) groups. Then independent t-test will be used to compare the mean change for the interventional groups against the mean change of the control group as an effect size. The level of significance will be set at a P-value < 0.0125 by using the Bonferroni correction formula for multiple outcomes (16, 29, 30). In this study, there are four outcomes of this single intervention, which included a mean change in prolapse symptoms and three components of prolapse quality of life (Paper IV). Therefore, the level of significance is obtained by dividing the usual P-value (0.05) by a number of statistics to be performed.

A summary of statistics will be computed both at the cluster-level and individual levels for both arms. The presence of cluster effects will be assessed and a multilevel analysis will be considered if a significant ICC value of > 0.5 is detected (31). As an alternative, since the outcome of this study is continuous data, both the cluster-level and individual-level analysis will produce the same result if the cluster size is equal. But if the cluster size is variable, an individual-level analysis weighted by cluster size will be done (20, 21).

This study will use stratified cluster randomization based on geographical locations. This may not balance all possible confounders, especially individual-level factors that may vary across strata. Therefore, the statistical technique of confounder control will be used to control possible confounders at the analysis stage. A Linear Mixed-Effect Model will be used to control confounders in multivariable linear regression. This analysis can increase the statistical power and preferable than the general equation estimation model (GEE) (32). Multicollinarity of the independent variables will be checked before fitting the variable into multivariable linear regression in similar fashion with Paper-II.

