## Data Management and Analysis

Data will be entered into Epidata version 3.1 and exported to STATA version 16 for analysis. The entered data will be cleaned and recoded before analysis. If there is any missing data, multiple imputation methods will be used to manage the missing data.

Before performing the main analysis, data will be weighted using the sample selection probability and the weighting class adjustment method to control for selection bias and non-response bias respectively ([147](#_ENREF_147), [148](#_ENREF_148)) based on the auxiliary data collected for the Demographic and Health Survey by Hawassa University.

The nature of the data and its distribution will be checked to identify any special distribution. For categorical data, its frequency will be run and checked for any unusual distribution. For continuous data, both statistical methods (mean, standard deviation, median, Skewness, and kurtosis); and graphical presentations (histogram) will be used to check its normal distribution. A mean and standard deviation will be reported for normally distributed data, while the median and interquartile ranges will be reported for non-normally distributed data.

The primary outcome in this study is the presence of anatomical pelvic organ prolapse, which is pelvic organ prolapse of stage I or more prolapse diagnosed through pelvic examination.

To identify predictors of POP, initially, data stratification will be done to identify possible confounders and effect modifiers ([149](#_ENREF_149)). Variable are considered confounding when their crude result (unadjusted odds ratio) is different from Mantel-Haenszel (M-H) (adjusted odds ratio) on stratified data ([150](#_ENREF_150)). An effect modifier is considered when the odds ratio of a variable is different across the strata.

In addition, the multicollinarity of the independent variables will be checked before the variable is fitted into multivariable logistic regression. In the multiple linear regression model, the variance inflation factor (VIF) > 1 and tolerance statistics < 0.1 show the presence of multicollinarity. The variance inflation factor (VIF) of 1-5 shows moderate multicollinarity, while VIF >5 shows high multicollinarity. In this analysis, variables with high multicollinarity will be omitted from the analysis ([151](#_ENREF_151)).

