## Data Measurements

Study participants’ adherence to training protocol will be evaluated at each follow-up time (week 2, 6, 10, and 15). At week two, women will be assessed for adherence to pelvic floor muscle exercise in the last two weeks (a few days per week, once per week, a few times a week, once a day, three times a day). At weeks six, 10, and 15, they will be assessed for adherence to pelvic floor muscle exercise in the last four weeks using similar questions used on week two (a few days per week, once per week, a few times a week, once a day, three times a day). In addition, they will be assessed for improvement in prolapse quality of life at 10 and 15 weeks. At the end of six months, the overall adherence to training protocol will be evaluated from their dairy or report of pelvic muscle trainer. Women’s adherence to training protocol is considered adequate when they complete at least 80% of the training sessions (24).

Prolapse quality of life will be measured for each three components of the tool separately. Each component will have a score of zero (0) to 100. The mean change of each component will be evaluated at the end of six months for both arms. The mean change will be compared between the two groups (intervention and control groups) to measure the effect of Pelvic Muscle Training. The secondary outcome, women’s perceived improvement after the intervention will be measured as improved, the same, or worsened based on Patient Global Impression of Improvement (PGI-I).

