**PART-V: POP-SS**

**Direction**

The following seven questionnaires are standard tools used to measure prolapse symptoms. Each item/question has 0 to 4 possible response scales. Inform the participant how to give a rate for each item based on how often she felt the prolapse symptom in the last four weeks (Put ‘X’ in the right box under each response scale).

Dear participant, please tell me how often did you feel the following POP symptoms in the last four weeks? (Please give the rating scale as follows: 0= never felt symptom in the last four weeks, 1= occasionally, 2= sometimes, 3= most of the time and 4= all of the time)

| **S.no** | **POP-Symptoms** | **0**  never felt symptom in the last four weeks | **1**  occasionally | **2**  sometimes | | **3**  most of the time | **4**  all of the time |
| --- | --- | --- | --- | --- | --- | --- | --- |
|  | A feeling of something coming down from or in your vagina? |  |  |  | |  |  |
|  | An uncomfortable feeling or pain in your vagina which is worse when standing? |  |  |  | |  |  |
|  | A heaviness or dragging feeling in your lower abdomen/tummy? |  |  |  | |  |  |
|  | A heaviness or dragging feeling in your lower back? |  |  |  | |  |  |
|  | A need to strain (push) to empty your bladder? |  |  |  | |  |  |
|  | A feeling that your bladder has not emptied completely? |  |  |  | |  |  |
|  | A feeling that your bowel has not emptied completely? |  |  |  | |  |  |
|  | Which of the symptoms above (questions 1–7) causes you most bother? | ……………. | | | | | |
|  | For how long have you felt one of the most chronic symptoms? | ……… | | | | | |
| **Patient Global Impression of Change questionnaire**  Ask the following questions only at end-line assessment (after intervention). Both the control and interventional group participants will be asked at the end of six months. | | | | | | | |
|  | How do you Perceive the change in prolapse since the start of the intervention? | | | | 1= Very much improved  2= Much improved  3= Minimally improved  4 = No change  5= Minimally worse  6= Much worse  7= Very much worse | | |

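### The analysis called intention-to-treat excludes enrolled women with no follow-up, a condition met only after allocation, and the protocol does not define follow-up

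*Protocol*

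**What the plan says.** Paper-III, Data Management and Analysis, announces an intention-to-treat analysis at six months and then defines who is in it: "This analysis will include all women included in the trial study at the beginning and who attended at least one follow-up". The same section says "Data entry, cleaning, missing data management and descriptive data presentation is similar with Paper-II", and the Paper II section it points to says "If there is any missing data, multiple imputation methods will be used to manage the missing data". Paper-IV, Data Management and Analysis, adopts the Paper-III procedure, so the definition also governs the three quality-of-life components.

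Follow-up is not defined. The relevant text elsewhere is as follows.

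- Paper-IV, Data Measurements, says that adherence to training "will be evaluated at each follow-up time (week 2, 6, 10, and 15"), so there the word means the clinic visits.
- Paper-III, Description of Intervention, sets out those visits: "They will be invited to attend five visits (at weeks 0, 2, 6, 10, and 15) at a nearby health facility". The paragraph opens "In the interventional group, at the initial visit, women will be informed about their stage of POP". No visit schedule is given for control women.
- Paper-III, Data Collection Tools and Procedure, says of the end-line: "After six months of intervention, the same data collectors of the baseline data will go to the house of the study participants". Annex II, Part V, confirms for the global-impression item: "Both the control and interventional group participants will be asked at the end of six months".
- Data Quality Control and Ethical Considerations promise home visits for women who miss appointments, without limiting this to one arm.
- Table 5 budgets follow-up transport for 136 women over four rounds.

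**The concern.** An intention-to-treat set is fixed by allocation. Here enrolment is joined by *and* to something that happens later, so the set depends on post-allocation behaviour. Women know whether they are being trained, so attendance may depend on arm and on how symptoms are going. Removing non-attenders can then break the comparability that cluster randomisation was meant to give, and a reader of the report would be told that the analysis was intention-to-treat when it was not.

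The clause also works against the rest of the plan. Multiple imputation is the planned way to keep women whose six-month score is missing. The attendance condition takes some or all of those women out before imputation can apply. The definition touches all four outcomes tested at 0.0125: the symptom score and the three quality-of-life components.

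**Working it through.** **The plan's own allowance.** Paper-III, Sample Size Determination, gives mean changes of 3.16 (SD 4.78) and 0.12 (SD 3.86), 99% confidence, 80% power and 16% refusal and loss. With the usual two-means formula:

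- n per arm = (4.78² + 3.86²) × (2.576 + 0.842)² / 3.04² = 47.70
- total with the allowance = 2 × 47.70 / 0.84 = 113.6, against the stated 113.4

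The figure reproduces closely. Refusal and loss are already allowed for in the sample size, so the exclusion is not needed to protect it.

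**How many women could lack a six-month score.** The flow diagram gives 78 per arm, 156 in all. Taking the whole 16% as loss after enrolment, which is an upper bound because the protocol combines refusal and loss without a split:

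- 0.16 × 78 = 12.48 per arm without a score
- 78 − 12.48 = 65.52 per arm with a score
- 0.16 × 156 = 24.96 overall

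If some of the 16% is refusal at entry, fewer enrolled women are affected: half gives 6.24 per arm, a quarter 3.12.

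**What the clause does under each meaning of follow-up.**

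1. *Only the six-month interview counts.* The rule is the same in both arms. The set is the women with an end-line interview, and imputation has no lost woman's six-month score left to fill, though it could still cover missing items or covariates.
2. *Any contact after baseline counts, and only the trained arm has visits.* A trained woman has five chances to qualify (weeks 2, 6, 10 and 15, and the interview); a control woman has one. A trained woman seen once and then lost is kept and imputed. A control woman lost at month six is dropped.
3. *Any contact counts, and both arms have visits.* The rule is the same in both arms, but enrolled women with no contact are still dropped.
4. *Only the week 2 to 15 visits count.* A woman interviewed at six months who made no visit would be dropped although her score was observed, and the bound of about 12 no longer limits the exclusions. If controls have no visits, no control woman could qualify at all, so this meaning is workable only with visits in both arms.

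Under all four, an enrolled woman can leave the analysis because of something that happened after allocation.

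**Whether controls have visits.** For the trained arm only: the schedule sits in a paragraph opened for the interventional group, and the visits serve training and adherence checks. For both arms: Table 5 computes 136 × 200 × 4 = 108,800 Birr. The Description of Intervention uses 136 for the two groups together (the Summary gives 68 per arm, an older total than 156), and four rounds match the four visits after week 0. The home-visit wording in Data Quality Control and Ethical Considerations is also arm-neutral. The text does not decide between the two.

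**The case against.** The strongest reply is that this is a familiar modified intention-to-treat set with little practical effect. Missed appointments trigger home visits, so women with no follow-up at all should be rare. Unless only the clinic visits count, those excluded have no six-month score, so keeping them adds no observed outcome and relies on an imputation assumption. Much of this stands: the number excluded may well be small, and no effect on the result has been shown. It does not rescue the definition. A modified set should not carry the intention-to-treat label, the protocol does not say whether a home visit counts as attendance, and the planned imputation exists to retain such women.

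A reader might go further and infer that the rule certainly favours one arm, with an imbalance of up to about 12 women. The documents do not support that. The budget line and the arm-neutral wording point to visits in both arms. Even with visits only in the trained arm, the rule is equal if follow-up means the six-month interview. A difference of 12 would also need the whole 16% to be loss after enrolment and every lost trained woman to have attended a visit.

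**Conclusion.** The point holds in a limited form. The set labelled intention-to-treat is not one, because it excludes enrolled women on a condition met after allocation. This follows from the sentence itself and needs no assumption about the visit schedule. That the rule acts unequally by arm is a possibility the protocol leaves open, not an established fault.

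The size and direction of any bias cannot be derived. On 78 per arm and the planned 16%, at most about 12 women per arm, or 25 of 156, would lack a six-month score. That figure assumes that all of the 16% is loss after enrolment. It limits the exclusions only if the six-month interview counts as follow-up. If only the week 2 to 15 visits count, women with an observed score could also be dropped, and the protocol gives no number for them.

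**What to change.** In Paper-III, Data Management and Analysis, delete the attendance clause and write: *All enrolled women will be analysed in the arm of their cluster, whatever their attendance; missing six-month scores will be imputed by the planned multiple imputation.* Paper-IV inherits the change through its reference to Paper-III. This repairs the set definition under every meaning of follow-up, without first having to settle whether controls have visits.

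The cost is wording only, with no added visits or data. The downside is that women with no data after baseline must be imputed, which adds uncertainty and rests on the missing-data assumption. It does not remove bias if loss differs between the arms in ways the imputation cannot account for.
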